#### Secondary objectives

##### Feasibility and acceptability

Due to the preliminary nature of this study, no prespecified criteria have been defined to establish acceptability of the LIO intervention, or the feasibility of the study procedures. The following measures of feasibility and acceptability will be analysed

Recruitment and retentionDescriptive statistics of recruited participant numbers and demographics.Percentage of participants recruited completing each data collection time point.AdherencePercentage of participants completing all three expression sessions (a) within 20–30 min time frame and (b) in a private space.Blinded independent assessor review of texts to determine which prompt was being responded to.Linguistic inquiry word count (LIWC) analysis of expression session texts/transcripts^51^ to analyse percentages of emotion, self and prompt-related words. LIWC is a computer program that calculates word count, and percentages of words used that reflect different emotions, thinking styles and concerns.AcceptabilityDescriptive quantitative analysis of responses to the feedback form.Combined deductive and inductive qualitative thematic analysis of free-text responses to feedback form and interviews with patient, carer and staff participants.^52^ Data will be coded to the seven constructs of the theoretical framework of acceptability for healthcare system interventions (deductive component).^53^ Within each construct, further codes will be developed from the raw data (inductive component). DM will lead the application and development of codes. These will then be checked and adjusted by the research team (intercoder review and code testing), and data re-coded. This process will be repeated iteratively until code/theme saturation is reached.^54^

##### Impact on psychological and physical well-being

Inductive thematic analysis of interviews and feedback from free-text responses from patients, carer and staff participants. DM will develop codes from the raw data, to be checked and adjusted by the research team; data will be re-coded, checked and adjusted until code saturation is reached.Descriptive pre–post analysis of changes in outcome measures (Integrated Palliative Care Outcome Scale, Patient Health Questionnaire 9, Generalised Anxiety Disorder 7, Sleep Quality Scale, uptake on mental health services): mean and standard deviation of scores at each time point.Descriptive summary of number of adverse effects reported by clinical team and participants.

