### Data collection

#### Overview—group 1

Table 1 provides a detailed description of the participant timeline and outcome measures for Group 1 participants.

**Table 1 T1:** Group 1 participant timeline, outcome measures and analysis approach

Measure	Time points administered	Description	Data type	Analysis approach	Relevant research objective*
Demographics	Baseline	Approximate date of hospice referral, age, gender, ethnicity, marital status, religious background, level of education, type of care (eg, inpatient, outpatient, day care), diagnosis, mental health history and COVID-19 status.	Quantitative	Descriptive statistics	1. Feasibility and acceptability
Expression sessions	Three sessions over 2-week intervention period	Typed, handwritten or audio-recorded responses to three expression sessions that make up the LIO intervention.	Quantitative and qualitative	LIWC and BIR inductive thematic analysis (session 2)	Feasibility and acceptability Underlying mechanisms Exploratory objective (session 2)
Health-related outcome measures (see below for details)	Baseline, immediately after the final expression, and, 1 week, 4 weeks and 8 weeks after the final expression	See below for details.	Quantitative	Descriptive statistics and descriptive pre–post analysis	Feasibility and acceptability Impact on well-being Outcome measure selection Underlying mechanisms
Integrated Palliative Care Outcome Scale (IPOS)—patient version^56^		An updated, brief (10 questions, 17 items) version of the POS instrument. IPOS was developed specifically to capture a range of the most important concerns of people living with palliative-stage disease, covering symptoms, information needs, practical concerns, anxiety or low mood, family anxieties and overall feeling of being at peace. Items in question 2–9 are scored from 0 to 4, and overall scores can range from 0 to 68. Questions 1 and 10 are not scored.			
Patient Health Questionnaire 9^57^		A 9-item instrument developed to screen for major depressive disorder, and validated in palliative care populations.^58^ Items are scored 0 to 3, and it can be scored continuously or with validated cut-offs for mild (5 to 9), moderate (10 to 14), moderately severe (15 to 19) and severe depression (20 to 27).^59 60^ The cut-off for a depression ‘case’ is 10.			

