Generalised Anxiety Disorder 7^61^		A validated 7-item anxiety screening instrument that is used to screen for anxiety in palliative care settings. Items are scored 0 to 3, and total scores range from 0 to 21. Severity of anxiety symptoms can be classed as none (0 to 4), mild (5 to 9), moderate (10 to 14) or severe (15 to 21). The cut-off score for a generalised anxiety disorder ‘case’ is 10.			
Single-item Sleep Quality Scale^62^		A short, pragmatic, tool for assessing sleep quality that has been validated in people with insomnia and depression, selected to reduce burden on participants from lengthier alternatives such as the Pittsburgh Sleep Quality Index.^63^ A single Visual Analogue Scale asks respondents to rate their overall quality of sleep over the last 7 days on a scale of 0 to 10. Scores are used to categorise sleep quality as: terrible (0), poor (1 to 3), fair (4 to 6), good (7 to 9) and excellent (10).			
Uptake of existing mental health services		A 3-item form developed by our research team specifically for this study asking participants if they have ever (a) sought help from a healthcare professional for their mental health; (b) sought help from a healthcare professional for their mental health over the past 2 weeks; and (c) any plans to seek help from a healthcare professional for their mental health in the future. Response options are ‘yes’, ‘no’ or ‘prefer not to say’.			
Meaningfulness/ personal/mood ratings	Immediately after each expression session	A 3-item, 7-point Likert scale based on a measure used in a study testing a similar intervention,^64^ measuring how personal and meaningful participants’ felt their expression session was (not very personal/not very meaningful (−3) to (+3) very personal/very meaningful). The last item will be a mood check where participants are asked to rate how they feel on a 7-point scale (very sad (−3) to (+3) very happy).	Quantitative	Descriptive statistics	Feasibility and acceptability Impact on well-being Outcome measure selection Underlying mechanisms

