*The research team will have a dedicated study phone that a member of the research team keeps only on their person during working hours (09:00–17:00 Monday–Friday) and is kept in a secure locked cabinet outside of those hours. The phone will be checked once a day for recordings or photos received, at which point the recording will be transferred to the dedicated project file on Data Safe Haven and deleted from the phone.

#### Self-report measures—group 1

All self-report data is collected online using the Research Electronic Data Capture (REDCap) online survey platform.^47 48^ Group 1 participants will complete a demographics questionnaire at baseline (prior to receiving the intervention). They will also complete a series of health-related questionnaires at baseline and 1, 4 and 8 weeks after the final intervention session (secondary outcome measures). Group 1 participants will also be prompted to log in to the platform during or after each expression session to indicate they have completed the session, and (if they wish) to share their response with the research team. Directly after each expression session they will also be prompted to complete a short self-report questionnaire to monitor their mood, and perception of how meaningful and personal the session was (secondary outcome measures). After the final expression session, participants will also complete a feedback form (primary outcome measure).

#### Semi-structured individual interviews (primary outcome measure)—group 1

Semi-structured interviews (n≤15) will be conducted within 8 weeks of the participant’s final expression session. Interviews will be conducted by DM, following a topic guide to explore participants’ experience of the intervention and questionnaires, including whether they experienced any negative feelings during or after each expression, whether they found the intervention helpful and the appropriateness and relatability of the expression session prompts, expanding on the topics covered in the feedback form.

Interviews will take place virtually and will be audio-recorded using Microsoft Teams, to minimise face-to-face interactions in line with government COVID-19 guidance. Recordings will be transcribed verbatim for analysis; transcripts will be pseudonymised and personally identifiable information redacted from the transcript.

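### The mental-health service uptake form has three categorical items and no score, yet the plan summarises it by mean and SD

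*Protocol article*

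**What the plan says.** Under Secondary objectives, the paragraph on impact on psychological and physical well-being lists five measures for the descriptive pre–post analysis: IPOS, PHQ-9, GAD-7, the Sleep Quality Scale and service uptake. The list ends with a single rule for all of them: "uptake on mental health services): mean and standard deviation of scores at each time point".

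Table 1 describes the uptake measure as "A 3-item form developed by our research team specifically for this study". Item (a) asks whether the participant has ever sought such help. Item (b) is whether they have "sought help from a healthcare professional for their mental health over the past 2 weeks". Item (c) concerns "c) any plans to seek help from a healthcare professional for their mental health in the future". For the answers, the table states: "Response options are ‘yes’, ‘no’ or ‘prefer not to say". It gives scoring rules for the other four measures and none for this one.

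Table 1 schedules the health-related measures at: "Baseline, immediately after the final expression, and, 1 week, 4 weeks and 8 weeks after the final expression". The section on self-report measures for Group 1 gives a shorter list, without the immediate assessment: "health-related questionnaires at baseline and 1, 4 and 8 weeks after the final intervention session".

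**The concern.** A mean and SD need a number for each participant. The uptake form yields three nominal answers, one of which is a refusal. The plan does not say how they become a score, whether the three items are summed or averaged separately, or where a refusal goes. Two analysts could follow the sentence faithfully and report different values, and a change in the number of refusals could look like a change in behaviour.

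This matters because the study reports no tests, so the descriptive summary is itself the result. The section on choice of outcome measure then uses these pre–post results to judge which measures may suit a future evaluation. A summary that depends on coding is a poor basis for deciding whether to carry this form forward.

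**Working it through.** The article gives no figure on this point, so there is none to reproduce. The check sets the definition against the planned statistic and then works out which weeks the 2-week item covers.

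**1. Definition against statistic.** Inputs: three items, three response options and no score (Table 1); mean and SD of scores (paragraph on impact). The rule presupposes a score, and the table supplies none.

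**2. The most favourable coding.** Take one item with yes = 1, no = 0 and refusals set to missing. The mean is the proportion p answering yes. The sample SD is √[p(1 − p) · n/(n − 1)], which p and n determine completely. With n = 40 (the maximum for Group 1):
- p = 0.1 gives SD 0.30
- p = 0.3 gives SD 0.46
- p = 0.5 gives SD 0.51

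The SD adds nothing to p.

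**3. Dependence on the coding of refusals.** The counts and codes here are invented for illustration and do not come from the article. Suppose that 40 people give 12 yes, 24 no and 4 *prefer not to say*:
- yes 1, no 0, refusal missing: mean 12/36 = 0.33, SD 0.48 (n = 36)
- yes 1, no 0, refusal 2: mean (12 + 0 + 8)/40 = 0.50, SD 0.68
- yes 1, no 2, refusal 3: mean (12 + 48 + 12)/40 = 1.80, SD 0.61

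The answers are identical and the three summaries differ. The example shows only that the coding matters. It does not estimate any bias in this study.

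**4. Coverage of the 2-week item.** A questionnaire at week v after the final session looks back over [v − 2, v]. At v = 0, 1, 4 and 8 the windows are [−2, 0], [−1, 1], [2, 4] and [6, 8]. Within weeks 0 to 8 they cover 0–1, 2–4 and 6–8, so 1 + 2 + 2 = 5 weeks. Weeks 1–2 and 4–6 are uncovered: 8 − 5 = 3 weeks. Leaving out the immediate assessment changes nothing within weeks 0 to 8, because [−2, 0] lies before them. The calculation assumes questionnaires completed on schedule.

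**5. What the other items recover.** A repeated item (a) changes from no to yes for someone who first seeks help in an uncovered week. It cannot change for someone who had already answered yes. Item (c) records intentions, not uptake. Help-seeking can therefore go unrecorded only for people already at yes on item (a) whose later contacts all fall in the uncovered weeks.

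**The case against.** The best defence is that the sentence condenses the treatment of five measures, that a 0/1 mean is a legitimate proportion, and that the generic descriptive wording in Table 1 leaves room for counts and percentages. Part of this stands. A reader might infer that a mean of this form has no meaning at all. That goes too far, since under one natural coding it is the proportion answering yes. But the article does not state that coding, the SD would still be redundant, and refusals would still have no place. The generic wording in Table 1 does not override a specific sentence that names the form.

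A reader might also infer that the uncovered weeks are an error. The article does not support this. It nowhere promises continuous coverage, its question is whether measures change between set time points, and a fixed 2-week window gives comparable snapshots.

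Nor does it follow that three-eighths of help-seeking is lost. The form records persons, not contacts, so anyone with one contact in a covered week is counted. If contacts are assumed to follow a Poisson process with weekly rate r, the share of help-seekers missed by item (b) is e^(−5r)(1 − e^(−3r))/(1 − e^(−8r)). This is about 33% at r = 0.05, 17% at r = 0.25 and under 1% at r = 1, before item (a) recovers first-time seekers. The rates are assumptions, as the article gives none.

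Finally, distress does not depend on this form alone to come to light. Researchers contact participants at the end of each intervention week, adverse effects are summarised, and the interviews ask about negative feelings.

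**Conclusion.** The mismatch holds as written: the plan fixes a mean and SD for a measure that its own Table 1 defines as three categorical items without a score. The resulting value depends on an unstated coding, above all of *prefer not to say*. This rests only on the two places in the article and needs no assumption about the data.

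The size is modest. It affects one of five descriptive secondary measures in a single-arm study of up to 40 patients, and neither the feedback form nor the interviews. It should still be corrected, because the statistic is stated explicitly and the results feed the choice of future outcome measures.

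The 3 uncovered weeks out of 8 are correct arithmetic for item (b) with on-time questionnaires. They limit what may be read as uptake over the whole follow-up, and they justify an optional improvement only.

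**What to change.** **Correction.** In the paragraph on impact, exclude the uptake form from the mean/SD rule. State instead that, for each item and time point, n (%) will be reported for yes, no and *prefer not to say*, with refusals as their own category and missing forms counted separately. Add a baseline-by-follow-up cross-table for the 2-week item. The cost is one or two sentences, with no new data and no added burden on participants.

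**Optional improvement.** Ask the *ever* item at baseline only. At follow-up, replace it with a question on help sought since the last questionnaire, and keep the 2-week item for comparison with baseline. The form stays at three items and the uncovered weeks are closed. First-time help-seeking remains identifiable from the baseline answer together with the new item. The costs are one reworded item in the survey platform and unequal look-back periods: about 1, 3 and 4 weeks at the last three assessments, and longer after a missed one. The new item would therefore describe cumulative uptake and should not be compared across time points. If collection has already begun, the correction alone is enough, with a note that the 2-week item does not cover weeks 1–2 and 4–6.

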**Methods and analysis:**

A single arm, mixed-methods, multisite, longitudinal study. Up to 40 people living with a terminal illness under the care of hospices in England and Scotland will receive the online LIO intervention. LIO consists of 3, self-guided expression sessions over 2 weeks. The primary outcome measures are (1) a structured feedback form completed by participants after the final expression session; and (2) semi-structured interviews and focus groups with ≤15 patient participants, ≤30 hospice staff and ≤15 informal carers. These quantitative and qualitative data will be triangulated via process evaluation to inform optimisation of the intervention design. Secondary outcome measures include validated measures of physical and psychological health collected at baseline and after the final expression session (immediately, 1, 4 and 8 weeks after); and data on recruitment, retention and fidelity.

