### Participants

The study will be conducted in three population groups recruited from participating hospices:

#### Group 1

Up to 40 adults living with terminal illness receiving palliative care from a UK hospice (on an inpatient, day care, outpatient or community basis). A sample size of 40 is recognised by the National Institute of Health Research as being appropriate for intervention feasibility and pilot work that is not designed to evaluate efficacy.^36 37^

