##### Group 1 exclusion criteria

Not expected to survive for longer than 10 weeks (based on clinical judgement).Lack of capacity to give informed consent or may be expected to lose capacity to give informed consent within 10 weeks (based on clinical judgement).Known diagnosis or history of severe depression, suicidal tendencies, psychotic symptoms, severe mood disorders, mania, schizophrenia, psychopathic/borderline personality disorder, severe and episodic (type 1) bipolar (affective) disorder (that is not well controlled).Not able to understand and communicate in English.

#### Group 2

Up to 15 informal (adult friend or family) carers of Group 1 participants.

#### Group 3

Up to 30 paid or voluntary hospice staff involved in organisation, delivery or implementation of psychological and/or emotional support.

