	Acceptability: How acceptable is the intervention for people living with terminal illness receiving care from hospices, their informal carers and hospice staff? What factors affect its acceptability?	Group 1 feedback form Interviews and focus groups with Group 1, 2 and 3	Descriptive analysis and inductive thematic analysis coded to concepts in the TFA
Impact and mechanisms	Impact: What are the perceived benefits of the intervention from the perspective of people living with terminal illness, their informal carers and hospice staff? Are there any changes in scores of psychological and physical health measures before and after (immediately, 1, 4 and 8 weeks post intervention)?	Group 1 feedback form Interviews and focus groups with Group 1, 2 and 3 Physical and psychological health-related outcome measures and mood checks	Inductive thematic analysis Descriptive pre–post statistics
	Mechanisms of impact: What cognitive processes are taking place during each expression session? Are there any patterns in the characteristics of participants who perceive benefits?	Expression session texts Demographic questionnaires	LIWC Descriptive statistics
Contextual factors	What factors at political, economic, organisational and individual level affected, or might be expected to affect, the implementation and/or impact? What options are there to minimise any barriers to successful implementation?	Group 1 feedback form Interviews and focus groups with Group 1, 2 and 3 Researcher reflective notes and informal feedback from research sites; withdrawal questionnaire	Inductive thematic analysis

LIWC, linguistic inquiry word count; TFA, the theoretical framework of acceptability.

Analysis will be led by DM in iterative consultation with the research team and advisory group. Codes, themes, descriptive statistics, data integration and conclusions generated by DM will be checked at key stages throughout the project by the research team. This will help minimise any risk of a positivity bias arising from DM’s close connection to the intervention being developed, and help validate the integrity of DM’s interpretation of the data. Thematic analysis will be carried out using QSR International NVivo V.11.4 software.^49^ Quantitative responses will be summarised using SPSS V.24.^50^

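### The pre–post summary is named an analysis of change but fixed as separate means and SDs at each time point, so selective loss could pass for change

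*Protocol article*

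**What the plan says.** The section on impact on psychological and physical well-being announces a "Descriptive pre–post analysis of changes in outcome measures" and, after the colon, fixes it as the "mean and standard deviation of scores at each time point". The measures are IPOS, PHQ-9, GAD-7, the sleep scale and use of mental health services. Table 1 schedules them at "Baseline, immediately after the final expression, and, 1 week, 4 weeks and 8 weeks after the final expression".

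The result has two stated uses. The Impact row of Table 3 asks "Are there any changes in scores of psychological and physical health measures before and after (immediately, 1, 4 and 8 weeks post intervention". The section on choice of outcome measure draws on the same pre–post results, together with qualitative data, to suggest measures for a later evaluation.

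On losses, the feasibility section reports the percentage of recruits completing each assessment. Table 3 describes the demographics of those who completed the intervention and lists a withdrawal questionnaire as a source. The exclusion criteria remove people whom clinicians do not expect to live, or to keep capacity, beyond 10 weeks. The section on expression sessions says that suspected loss of capacity or severe distress leads to assessment, and that anyone found no longer eligible is withdrawn.

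**The concern.** A difference between two means equals the average change within people only if the same people contribute to both. Here that is unlikely to hold. A 2-week intervention followed by an 8-week last assessment gives about 10 weeks of follow-up in people with terminal illness. The survival criterion covers the same span and rests on clinical judgement, so it reduces loss without removing it. Withdrawal after loss of capacity or severe distress links leaving the study to the very states being measured.

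If the sicker or more distressed stop answering, PHQ-9, GAD-7 and IPOS means drift down (and the sleep mean drifts up) without anyone improving, and a real worsening can be hidden. A measure could then look responsive to the intervention only because its high scorers left. That would feed the change question in Table 3 and the selection of outcome measures. Separate SDs also do not give the SD of change, which a later trial would want to know.

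**Working it through.** **Inputs from the protocol.** Group 1 is "Up to 40 adults living with terminal illness receiving palliative care from a UK hospice", in a single arm. The summary is a mean and SD at each of five time points. PHQ-9 items are scored 0 to 3, and higher is worse.

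**Inputs the protocol does not give, so assumed.** The share lost (d), the baseline gap between those lost and those who stay (g), the SD, and the within-person correlation (ρ). The plan has no figure of its own to reproduce: the sample size rests on a convention described as "appropriate for intervention feasibility and pilot work that is not designed to evaluate efficacy".

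**Step 1: shift when nobody changes.** Let those who stay have baseline mean m and those lost have m + g.
- Baseline mean of everyone: (1−d)·m + d·(m+g) = m + d·g.
- Later mean of those still answering, with no individual change: m.
- Difference: −d·g.

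**Step 2: PHQ-9 illustration (points).**
- d = 20% (8 of 40 lost), g = 2: 0.2×2 = 0.4.
- d = 40% (16 of 40), g = 4: 0.4×4 = 1.6.
- d = 50% (20 of 40), g = 5: 0.5×5 = 2.5.

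Each is a fall in the mean, read as improvement. If g = 0 or d = 0 the shift is 0. If those lost began better off, g is negative and the sign reverses.

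**Step 3: the same on an SD scale.** With d = 20% and g = 0.25 SD the shift is −0.05 SD; with d = 50% and g = 1.0 SD it is −0.50 SD.

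**Step 4: a real worsening hidden.** Suppose everyone worsens by 0.3 SD and d = 50%.
- g = 0.5 SD: 0.3 − 0.5×0.5 = +0.05 SD, nearly invisible.
- g = 1.0 SD: 0.3 − 0.5×1.0 = −0.20 SD, an apparent improvement.

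**Step 5: what pairing does.** Restricted to people with both assessments, both means in Step 1 equal m, so the composition term is exactly 0.

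**Step 6: SD of change.** With equal SDs at both times, SD of change = SD×√(2(1−ρ)). For ρ = 0.3, 0.5, 0.7 and 0.9 this is 1.18, 1.00, 0.77 and 0.45 times the SD. The means and SDs at each time point cannot say which applies.

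**The case against.** The strongest reply is proportion. This is one descriptive component of a secondary objective. The primary outcomes are the feedback form and the interviews and focus groups, and the Design section rules out efficacy hypotheses and p-values. Impact and outcome-measure choice also draw on qualitative data, and no decision is tied to a change in means. That stands, and it limits the severity. It does not remove the mismatch, because the problem is bias in a description, not a matter of testing.

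The article also has partial safeguards: completion percentages, demographics of intervention completers, a withdrawal questionnaire, and exclusion of people with short expected survival or severe depression. These may reduce loss and narrow g. None of them shows whether those missing at follow-up had different baseline scores.

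A reader might infer more than the text supports in three ways:
- **That no within-person change will ever be computed, or that each mean certainly comes from a shrinking set.** The article names one summary, does not exclude others, and does not fix the analysis set. If the means were limited to people who answered every time, Step 1 would not arise, though the SD of change would still be missing. What can be said is that the stated computation is not the one its label promises.
- **That precision is lost by treating repeated means as independent.** The plan states no standard error, interval or such comparison, so there is nothing to correct.
- **That a repeated-measures mixed model is needed.** With at most 40 people, and some scores missing because of death, it would implicitly model scores after death, which is debatable here.

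**Conclusion.** The point holds as a mismatch between label and definition: the document calls the summary an analysis of changes and fixes it as a mean and SD at each time point. This is a stated computation, not a detail left to a fuller document, and nothing else in the article repairs it.

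Under the assumed PHQ-9 inputs, the shift with no individual change is 0.4 to 2.5 points. This rests on means taken over whoever answers and on selective loss. Neither the loss nor the gap is given in the document, so the real size and direction are unknown and could be nil.

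It should be fixed, as a nearly free improvement to a secondary descriptive analysis. It does not undermine the primary objective.

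**What to change.** Amend the definition in the section on impact on well-being so that, at each follow-up, the report gives for participants with both assessments:
- the number contributing;
- their own baseline mean;
- the mean and SD of within-person change, optionally with a 95% confidence interval and no p-value.

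The mean and SD at each time point can stay beside these. Add a table of baseline scores by whether each follow-up was completed, for participants whose data may be kept under their advance consent. Count deaths, withdrawals and other missing assessments separately.

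State two limits in the text: paired change describes only those still answering, and with one arm it cannot separate the intervention from the course of the disease.

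The cost is a few extra SPSS tables and some added wording. The scores are already collected; the only addition is a recorded reason for each missed assessment, for which a withdrawal questionnaire already exists in part.
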